# Guided self-determination-young versus standard care in the treatment of young females with type 1 diabetes: study protocol for a multicentre randomized controlled trial

**DOI:** 10.1186/s13063-017-2296-6

**Published:** 2017-11-24

**Keywords:** Type 1 diabetes, Adolescents, Person-centred care, Guided self-determination-young (GSD-Y), Female, Intervention

## Abstract

**Background:**

Female adolescents with type 1 diabetes mellitus (T1DM) have the most unsatisfactory glycaemic control of all age groups and report higher disease burden, poorer perceived health, and lower quality of life than their male counterparts. Females with T1DM face an excess risk of all-cause mortality compared with men with T1DM. New methods are needed to help and support young females with T1DM to manage their disease.

A prerequisite for successful diabetes management is to offer individualized, person-centred care and support the patient’s own motivation. Guided self-determination (GSD) is a person-centred reflection and problem-solving method intended to support the patient’s own motivation in the daily care of her diabetes and help develop skills to manage difficulties in diabetes self-management. GSD has been shown to improve glycaemic control and decrease psychosocial stress in young women with T1DM. The method has been adapted for adolescents and their parents, termed GSD-young (GSD-Y). The aim of this study was to evaluate whether an intervention with GSD-Y in female adolescents with T1DM leads to improved glycaemic control, self-management, treatment satisfaction, perceived health and quality of life, fewer diabetes-related family conflicts, and improved psychosocial self-efficacy.

**Methods/design:**

This is a parallel-group randomized controlled superiority trial with an allocation ratio of 1:1. One hundred female adolescents with T1DM, 15–20 years of age, and their parents (if < 18 years of age), will be included. The intervention group will receive seven individual GSD-Y education visits over 3 to 6 months. The control group will receive standard care including regular visits to the diabetes clinic. The primary outcome is level of glycaemic control, measured as glycosylated haemoglobin (HbA1c). Secondary outcomes include diabetes self-management, treatment satisfaction, perceived health and quality of life, diabetes-related family conflicts, and psychosocial self-efficacy. Data will be collected before randomization and at 6 and 12 months.

**Discussion:**

Poor glycaemic control is common in female adolescents and young adults with T1DM. Long-standing hyperglycaemia increases the risks for severe complications and may also have an adverse impact on the outcome of future pregnancies. In this study, we want to evaluate if the GSD-Y method can be a useful tool in the treatment of female adolescents with T1DM.

**Trial registration:**

Current controlled trials, ISRCTN57528404. Registered on 18 February 2015.

**Electronic supplementary material:**

The online version of this article (doi:10.1186/s13063-017-2296-6) contains supplementary material, which is available to authorized users.

## Background

### Diabetes and female adolescents

It is well established that poor glycaemic control during adolescence and young adulthood increase the risks of acute and long-term diabetes-related complications [1]. Recommended treatment for children and adolescents with type I diabetes mellitus (T1DM) is multiple daily injections (MDI) or continuous subcutaneous insulin infusion (CSII) [2]. Intensive diabetes management has been in the clinical routine in Sweden for many years. The Swedish recommended level of glycaemic control, measured as glycosylated haemoglobin (HbA1c), for children and adolescents (<18 years) has recently changed (in 2017) from 57 mmol/mol or below to 48 mmol/mol or below without increasing the number of hypoglycaemic episodes [2]. For adults, the corresponding target is HbA1c < 52 mmol/mol [3]. To reach the recommended level it is necessary to measure blood glucose frequently or to use continuous or flash glucose monitoring (CGM/FGM). In Sweden, only around 55% of the paediatric population with T1DM reached the former HbA1c target of < 58 mmol/mol [4]. After starting school, at 7 years of age, HbA1c tends to increase with age and female adolescents have the most unsatisfactory glycaemic control of all age groups [4]. A similar pattern has also been found in other European countries [5]. Girls with T1DM report a higher disease burden, poorer perceived health, and lower quality of life (QoL) than boys [6–8], and females with T1DM face a 40% excess risk of all-cause mortality compared with men with T1DM [9]. Furthermore, women with T1DM have a significantly higher healthcare expenditure than men [10]. A nationwide study from Sweden demonstrated that female sex and high HbA1c adjacent to the diagnosis of T1DM are risk factors for poor control in young adults with increased prevalence of nephropathy and retinopathy [11]. This is in line with findings from previous studies reporting that female gender is a risk factor for microvascular complications [12–14]. Girls with T1DM have significantly higher mean body mass index (BMI) at follow-up compared with their male counterparts [15], and an elevated BMI is associated with higher levels of HbA1c [15]. Furthermore, high pre-pregnancy BMI is an important risk factor for adverse outcome in type 1 diabetic pregnancies [16]. In the report from the Public Health Agency of Sweden 2016, female adolescents (16–29 years) reported a higher degree of both mild and severe anxiety compared with their male counterparts [17]. In females with T1DM, but not in males, means of communication and a perception of being able to control the disease have been shown to be important contributing factors for achieved level of glycaemic control [18]. Furthermore, the coping strategy “ventilating negative feelings” was associated with poor metabolic control among females [18]. Active coping, in this case referring to how to rationally manage a problem, was found to be related to improved metabolic control in adolescents with T1DM [19]. On the other hand, emotion focused coping, such as behavioural disengagement and aggressive coping, was related to poor metabolic control [19]. This emphasizes the importance of finding out the patient’s coping strategies, views, and perceptions of her diabetes.

### Adolescence

During adolescence the needs of healthcare are distinctly different from the needs of younger children and adults. The patient’s need for liberation and self-determination often interferes with diabetes self-management [20] which makes diabetes treatment challenging [21]. Both treatment-related factors and factors related to the individual influence metabolic control. It is recommended to provide health education strategies that optimize self-care. This can involve problem solving, clarifying priorities and target setting, as well as using new technology [22]. Development of equipment for glucose monitoring and insulin delivery has significantly improved the outcome for patients with T1DM. However, adherence to a complex, demanding, and intensive diabetes regimen requires life-long changes in behaviour and involves daily performances of several unpleasant tasks. In the aspect of QoL, it may be just as important to meet the adolescent’s developmental needs as any other diabetes-specific treatment [20, 23].

Adolescents with chronic conditions have been found to have fewer protective factors and more risky behaviour compared to their healthy peers [24]. Family support is an important protective factor in reducing risky behaviour [24]. Communication within families and maintenance of parental support have been shown to contribute to metabolic control in adolescents with T1DM [22, 25, 26], but the patient’s own commitment is crucial for successful management. It is more common that children have high HbA1c in families who have many diabetes-related conflicts [27]. Healthcare professionals should support adolescents and parents to find both new means for parental involvement and levels of communication that suits both the adolescent and the parents [23, 28].

Finding out what is unique for the patient in a person-centred approach and in aspects of developmental, individual, and family factors is of great importance.

### Guided self-determination-young

Person-centred care aims at engaging the person as an active partner in his/her own care and treatment and at supporting the patient’s own ability to manage the disease in a positive way [29]. Guided self-determination (GSD) is an example of an empowerment-based education method providing person-centred care. By using worksheets for reflection and problem-solving, GSD intends to guide the patient to become self-determined and to obtain skills for better diabetes self-management [30]. GSD has been demonstrated to improve glycaemic control and decrease psychosocial stress in young adult women (18–35 years) with T1DM [31]. The method has been adapted to adolescents, termed guided self-determination-young (GSD-Y) [32–34], but data on its effect on glycaemic control and other outcomes in this age group are scarce [35]. There is only one study of limited size (*n* = 57) investigating the effect of GSD-Y in girls and boys with T1DM (aged 13–18 years) [32]. In that study, no significant reduction in HbA1c was demonstrated but the intervention improved the patient’s motivation for diabetes self-management [32]. Preliminary results from an ongoing study on adolescents aged 12–18 years starting treatment with CSII [34, 35] show decreased diabetes-related family conflicts and a larger decrease in HbA1c in the intervention group 6 months after intervention with the GSD-Y method.

It is clear that we need to find new methods to help and support young females with T1DM to manage their disease, and previous studies with the GSD method have shown positive results, especially for young adult females. Thus, the GSD method is a promising tool.

### Study aim and hypothesis

The aim of this study is to evaluate if an intervention with GSD-Y, in female adolescents and their parents, leads to improved glycaemic control, self-management, treatment satisfaction, perceived health and QoL, fewer diabetes-related family conflicts, and improved psychosocial self-efficacy.

Our hypothesis is that the GSD-Y method can improve glycaemic control, perceived health, and QoL among young females with T1DM.

## Methods/design

### Study design and setting

This is a parallel-group multicentre randomized controlled trial with an allocation ratio of 1:1 and a superiority framework. The study will be conducted at the Unit for Youth at Sachs’ Children and Youth Hospital (aged 15–20 years old) and at the outpatient diabetes clinic at Ersta Hospital (aged 18–20 years old) in Stockholm, Sweden. A flow chart of the study is presented in Fig. 1. The GSD-Y method was tested in six patients at our clinic before the study started and the questionnaires that we use are all validated and have been used by our research group in previous studies.

**Fig. 1 Fig1:**
[figure not shown]
Flow chart for GSD-Y versus standard care. *ANOVA* analysis of variance, *CGM* continuous glucose monitoring, *DFCS* Diabetes Family Conflict Scale, *DTSQ* Diabetes Treatment Satisfaction Questionnaire, *FGM* flash glucose monitoring, *GSD*-*Y* guided self-determination-young, *HbA1c* glycosylated haemoglobin, *SMBG* self-monitoring of blood glucose, *Swe*-*DES 23* Swedish Diabetes Empowerment Scale

This paper follows the Standard Protocol Items Recommendations for Interventional Trials (SPIRIT) guidelines for intervention trials. The SPIRIT checklist and figure are included as Additional file 1 and Fig. 2.

**Fig. 2 Fig2:**
[figure not shown]
SPIRIT figure. *CGM* continuous glucose monitoring, *DFCS* Diabetes Family Conflict Scale, *DTSQ* Diabetes Treatment Satisfaction Questionnaire, *FGM* flash glucose monitoring, *GSD*-*Y* guided self-determination-young, *HbA1c* glycosylated haemoglobin, *SMBG* self-monitoring of blood glucose, *Swe*-*DES 23* Swedish Diabetes Empowerment Scale

### Participants

One hundred female adolescents with T1DM, aged 15–20 years, with parents (if participants are under 18 years of age) will be included. Exclusion criteria includes a diagnosis of diabetes within the past year, or HbA1c below the national recommended level for adults (< 52 mmol/mol) and if the adolescent or their parents have difficulties understanding Swedish. The usual healthcare provider (HCP) at the diabetes outpatient clinic, supervised by JH, will enrol participants in the study. In Sweden, patients with T1DM are only treated at specialist centres and no concomitant care is involved in the diabetes treatment. Written informed consent for participation in the study will be obtained from adolescents and their parents (if participants are under 18 years of age) and given to the HCP and then collected by JH or [name] and stored in a locked and fireproof cabinet. Participants will be randomized to either the intervention or control group after filling in the written informed consent and the baseline questionnaires.

### Randomization

Participants are randomized using opaque sealed envelopes containing a once-folded piece of paper with written information on which group the participant is randomized to: intervention or control group. The envelopes are prepared by two researchers not involved in the study using coin tossing. The researchers will toss a coin and then, according to either “heads” or “tails”, put a once-folded piece of paper, with written information on either intervention or control group, in an opaque envelope and seal it. This coin-tossing will continue in blocks of two, i.e. one out of the two first envelopes will contain a paper that says “intervention” and the other envelope will contain a paper that says “control”. The first two envelopes will then be marked by “1” and “2” but it will be unknown which one contains which group. The coin-tossing continues until 100 envelopes are prepared and marked with the numbers “1” to “100”. At each randomization, the envelopes will be randomly mixed in groups of three with the number on the envelope face down, and the participant will choose one of these envelopes herself.

The structure of the GSD-Y method does not allow further blinding of group allocation after the randomization process.

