### Intervention

Individuals in the intervention group will receive seven individual GSD-Y visits (of 1–1.5 h) with a facilitator (either a diabetes nurse or a physician) over 3 to 6 months. The facilitator is educated in the GSD-Y method. The GSD-Y method includes that the participant works with structured reflection sheets. By filling in reflection sheets before each visit and using their own words and drawings, participants systematically explore and express their own experiences and difficulties with diabetes in daily life. In addition, if the participant is under 18 years of age, her parents will be offered one individual visit and one visit together with the participant according to the GSD-Y method. The topics for the different visits are presented in Table 1. The first reflection sheet will be sent or given to the participants before the first visit. For subsequent visits, the reflection sheet for the next meeting will be distributed at that visit and completed before the next visit. In the dialogue between the participant and the facilitator, the facilitator uses different communication methods including mirroring, active listening, and value-clarifying responses. Those participants who have taken part in the first five GSD-Y visits will be considered to have completed the education. Visits are booked in consultation with each participant and, if a participant misses out of a visit, she will be offered another appointment provided she wants to continue with the study.

**Table 1 Tab1:** Overview of reflections sheets

Visit 1	Your life with diabetes from the beginning to now
	Written invitation to work together in a new way
	Two ways of looking at glycosylated haemoglobin (HbA1c)
	Agreement on things to work on
Visit 2	Your life with diabetes from the beginning to now
	Important events and periods in your life
	What do you find difficult at present living with your diabetes?
	Your plans for changing your way of life
Visit 3	Values and opportunities
	Unfinished sentences: needs, values, experiences, and opportunities
	Individual visits for parents are offered
Visit 4	Diabetes in your life
	A picture or expression describing your life with diabetes
	Room for diabetes in your life
	Shared responsibility between adolescent and parent for diabetes in daily life
	Common name for difficulty in your life with diabetes
	Agreement on things to work on until next visit
Visit 5	Problem identification and problem solving
	Current problem solving

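### Pairs of envelopes drawn from mixed threes leave the next allocation guessable above chance, and the text does not say how threes are refilled or how the two clinics share the series

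*Protocol article*

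**What the plan says.** The protocol article's Randomization section describes opaque sealed envelopes prepared by two researchers outside the study. A coin toss orders each pair: "This coin-tossing will continue in blocks of two", with one intervention and one control paper per pair. There is one series, running from 1 to 100: "The coin-tossing continues until 100 envelopes are prepared and marked with the numbers". For the draw, "At each randomization, the envelopes will be randomly mixed in groups of three with the number on the envelope face down". It is the participant who makes the pick. On what follows, the section says: "The structure of the GSD-Y method does not allow further blinding of group allocation after the randomization process".

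Under Participants, "The usual healthcare provider (HCP) at the diabetes outpatient clinic" enrols, and consent and baseline questionnaires come before the draw. Under Study design and setting there are two sites. One takes ages 15–20, and the other is "at the outpatient diabetes clinic at Ersta Hospital (aged 18–20 years old) in Stockholm, Sweden". Under Intervention the content changes at 18: "if the participant is under 18 years of age, her parents will be offered one individual visit and one visit together with the participant".

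The main comparison, under Statistical analysis and power calculation, is an unpaired t test or Mann-Whitney test with no centre term. The article does not say whether a drawn envelope is replaced to restore three, or how the single series is divided between the clinics.

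**The concern.** Three stated features combine: a very small published block size, open allocation, and enrolment by a provider who already knows the patient. A provider who can predict the next arm better than chance can decide whom to approach, and when, according to motivation or HbA1c. Taking consent before the draw does not prevent this, because the selection happens earlier. Adjustment for measured baseline values does not remove selection on unmeasured motivation.

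Balance is a separate and smaller matter. The only series described has no strata, although the clinics differ in age range.

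**Working it through.** **Inputs.** From Randomization: pairs, one series of 100, draw from three. From Statistical analysis and power calculation: difference 6 mmol/mol, SD 10, 80% power, alpha 0.05, 44 per group, 12% dropout. Assumed, because not given: two-sided alpha, the smaller clinic's share (20–40%; 10–40% where envelope numbers are tracked), and half the participants under 18.

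**The plan's own figure.** n = 2(1.960 + 0.842)² × 10² / 6² = 43.6, so 44 per group. 88 / (1 − 0.12) = 100. It reproduces.

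**Guess rate with all earlier allocations known (chance 50%).**

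1. *Plain pairs.* First of the pair 1/2, second certain: (0.5 + 1)/2 = 75%, with 50% certain.

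2. *Three refilled after each draw* (the reading closest to the wording). At alternate draws, every pair that has entered is complete, so the running difference between arms shows what the three envelopes hold: 2:1 (guess right with probability 2/3) or 3:0 (certain). Next, two known envelopes and one new unknown envelope are on the table. If the two are one of each arm, the guess is 1/2. If they are the same arm, it is 2/3 + (1/3)(1/2) = 5/6.
 - From 2:1, the next complete three is 3:0 with probability (1/3)(1/6) = 1/18. From 3:0 it is 3:0 again with probability 1/6. In the long run 2:1 holds 15/16 of the time and 3:0 holds 1/16.
 - Complete draws: (15/16)(2/3) + 1/16 = 0.6875.
 - Other draws: the two known envelopes differ with probability (15/16)(2/3) = 0.625, so 0.625 × 0.5 + 0.375 × 5/6 = 0.625.
 - Mean (0.6875 + 0.625)/2 = 65.6%, with (1/16)/2 = 3.1% certain. Simulating the full 100, where the last draws are not refilled, gives 66% correct and 4% certain.

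3. *Three used up before the next.* The pattern repeats every six envelopes. Success by draw, from arm counts, is 1/2, 2/3, 2/3, 2/3, 2/3, 1. The sum is 4.167, and 4.167/6 = 69.4%. Certain calls are (1/3 + 1/3 + 1)/6 = 27.8%. Simulation gives 70%. If envelope numbers are also tracked, it is 72% correct and 34% certain.

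**Guess rate with only one's own clinic known.** With a shared stack, staff at the larger clinic guess 54–56% from arm counts (simulated, smaller clinic 20–40%). If they also track envelope numbers, the rate is 61–70% (smaller clinic 10–40%).

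**Benchmark.** Permuted blocks of known size b give b/2 + (2^b / C(b, b/2) − 1)/2 correct per block: 1.5/2 = 75% for b = 2, 2.833/4 = 70.8% for 4, 4.1/6 = 68.3% for 6 and 5.329/8 = 66.6% for 8. Sizes 2, 4 and 6 in equal numbers give (1.5 + 2.833 + 4.1)/12 = 70.3%. Sizes 4, 6 and 8 give (2.833 + 4.1 + 5.329)/18 = 68.1%.

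**What a guess rate could be worth (illustration).** If staff steer patients by ±d mmol/mol in later HbA1c toward the likelier arm, the spurious difference is 2d(2g − 1) at guess rate g. With g = 0.658 and d = 3 it is 6 × 0.316 = 1.9, against a target of 6; simulated type I error is about 15%. With g = 0.54–0.56 it is 6 × 0.08 to 6 × 0.12, or 0.5–0.7. The documents give no value for d.

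**Balance with one shared stack** (simulated, each participant assigned to the smaller clinic at random with the assumed share). The overall split is 50:50 at 100, and under the two mixing readings the running imbalance never exceeds 3.

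| Assumed share at smaller clinic | Split of 60:40 or worse there |
|---|---|
| 20% | 35–37% of trials |
| 30% | 21–22% |
| 40% | 11–12% |

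Within an age group holding half the participants, the same split occurs in about 5–6% of trials.

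**The case against.** The strongest defence is that mixing in threes is a real safeguard. It brings guessing down from 75% to about 66% on the most natural reading, which is below ordinary fixed blocks of four (70.8%) or six (68.3%). The envelopes are opaque and sealed, outsiders prepared them, the numbers lie face down, and consent precedes the draw. All of this stands, and it limits tampering. It does not remove prediction from past arms.

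It also stands that the 66–70% figures assume knowledge of every allocation at both clinics, which the article does not state. The two limbs depend on opposite readings as well. A shared stack weakens guessing within a clinic but leaves clinic balance open. Separate runs per clinic keep guessing strong but nearly balance each clinic. The worst of both cannot be claimed at once.

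A reader might infer more than the text supports:

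- *That most allocations are known in advance.* On the refilled reading only about 4% are certain.
- *That the missing strata bias the result.* Chance imbalance by centre costs precision only, and serious age imbalance is unlikely.
- *That no allocation record can exist.* The envelopes are numbered and, under Data management, participants are coded at randomization. A condensed article need not describe a log.
- *That envelopes are opened in front of clinic staff.* The text does not say where they are opened.

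**Conclusion.** The point holds in moderate form. The procedure as written leaves the next arm predictable above chance on both mixing readings: about 66% (refilled) or 69–70% (used up) with full knowledge of past allocations, and 54–56% from own-clinic arm counts on a shared stack. Which figure applies cannot be settled, because refilling and sharing are unspecified. Whether any selection would follow is not known; the scheme leaves room for it.

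If the stack is shared, balance within the smaller clinic is unprotected to the extent tabulated, given the assumed shares. The overall 1:1 ratio is safe. This should be fixed, with moderate confidence. It does not show that the trial's comparison is invalid.

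**What to change.** For participants still to be enrolled, replace the envelope draw with a computer-generated list stratified by centre, using larger randomly varying blocks (for example 4, 6 and 8) whose sizes are not disclosed to clinic staff. The uninvolved researchers should hold the list and release each allocation only after consent and baseline are logged. Include centre in the primary model, which means a linear model in place of the plain two-group test. Stratifying by age group is optional.

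The block sizes are not themselves the remedy. Varying blocks of 2, 4 and 6 give about 70% to a guesser who knows the scheme, no better than now, and even 4, 6 and 8 give 68.1% to someone who tallies every allocation in the stratum. Stratifying by centre also makes a clinic's own tally complete, which is a reason to prefer the larger blocks. The gain comes from staff not knowing when a block closes, from release outside the clinic after enrolment is fixed, and from protected balance within clinic.

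For participants already randomized, state whether threes were refilled or used up and how the series was divided between clinics.

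Cost: a short amendment, no extra patients, and two allocation methods in one trial, handled by a before/after sensitivity check. Trial status gives recruitment from May 2017 to about January 2020 and a protocol version of October 2017, so most of the planned recruitment period still lay ahead.
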